### Outcomes

The primary outcome is the annualised rate of medically attended ALRIs during the intervention period of 6–12 months when the participants received the trial medications. Outcomes are assessed at 6 and 12 months for those who received 6 and 12 months of study trial medication, respectively.

Secondary outcomes are the rates and proportions of children with:

ALRI hospitalisations during the intervention period at 6–12 months.ALRI hospitalisations during and post-intervention (at 24 months post-commencement of trial medications).Adverse events (eg, nausea, vomiting, diarrhoea and rash).Nasopharyngeal colonisation by macrolide-resistant respiratory pathogens at baseline, (6), 12, 18 and 24 months.Chronic respiratory symptoms/signs suggestive of underlying CSLD or bronchiectasis at 24 months.ICER on the potential benefits (in terms of savings in hospitalisations and medical evacuations, and other associated costs to health services and patients) of azithromycin compared with placebo over the additional costs of administering the drug.

### Data monitoring, management and analyses

All study participants are assigned a unique study identifier at enrolment, which is the primary identifier on all study records including bio-specimen labels throughout the trial. Confidentiality is maintained in accordance with GCP guidelines and with respective HREC requirements at each site. All identifiable data from study participants are retained on a password-protected REDCap database and in locked filing cabinets at each study site. Each site is responsible for data entry. Data management is overseen by the principal investigator ([name]) at Menzies. Access to these data is only provided to immediate members of the research team except if requested by legislative or regulatory agencies, or by the respective HREC at each site.

All adverse and serious adverse events are monitored by an iDMC which was established prior to commencing the trial. Reference groups at each site oversee cultural aspects of the RCT.

A detailed statistical analysis plan will be prepared and approved by the chief investigators and the iDMC prior to undertaking the final analysis. Data will be audited, cleaned and locked before any analyses are undertaken. The investigators will only see analyses of pooled data until the statistical analysis code has been written (on pooled data) and agreed, and the trial has terminated. At this point, unblinding of investigators will occur. The analysis will be directed by a biostatistician. Results will be reported in accordance with the Consolidated Standards of Reporting Trials guidelines. We will use an ‘intention-to-treat’ approach for the primary analysis. Missing data will not be imputed. No interim analysis is planned. Any post hoc analysis or unplanned analyses will be described clearly.

#### Primary aim

To determine the efficacy of azithromycin, the annualised rate of medically attended ALRIs in those randomised to receive 6–12 months of azithromycin will be compared with those receiving placebo (controls). A negative binomial regression model and incident rate ratio (IRR) 95% CI, including treatment group and the number of months taking treatment in the study included as an offset, will be used to determine between-group differences with 95% CIs. Subgroup analyses will be done for age (≤12, >12 months) and adherence (≤ or >70%).

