## Methods and analysis

### Design

The azithromycin to **‘**Prevent rEcurrenT Acute Lower Respiratory Infections’ (PETAL) trial is a parallel (1:1), double-blind, placebo-controlled, multicentre, international superiority RCT (figure 1). It aims to determine whether 6–12 months of azithromycin following ALRI hospitalisation reduces subsequent ALRIs and improves other clinical and economic outcomes. The first participant was randomised in October 2020, and we anticipate that recruitment will be completed by February 2025.

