#### Randomisation, allocation concealment and blinding

Randomisation is undertaken by each site’s pharmacy representative who allocates participants to a treatment according to a randomisation sequence. Each site has two randomisation sequences; one stratified by site and the other by whether the child has had a prior ALRI hospitalisation or not. An opaque envelope with the corresponding respective randomisation number is then opened to reveal treatment allocation as one of eight bottle letters (A–H), four allocated to azithromycin and four to placebo. The randomisation sequences were generated by an independent statistician using permuted blocks.

The first dose of trial medication is given in hospital and then dispensed weekly by either a member of the research team, primary health clinic staff or family member (whichever is appropriate) for each site. Adherence is monitored by the research team in weekly medication logs based on parent reports. People masked to the treatment allocation are those (1) receiving the treatment, (2) administering the treatment, (3) assessing the outcomes and (4) analysing the data.

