##### Sample size

Based on our primary outcome (rate of medically attended ALRI), 80 children per group (total sample size n=160, including 15% attrition) will provide 90% power to detect a 40% reduction (IRR=0.6) in medically attended ALRI episodes per child-year. We assumed a rate of three medically attended ALRI episodes per child-year in the control group, based on community presentations for respiratory illnesses in our setting,^33^ a shape parameter of k=0.4, and a two-sided significance level of 5%. Children who are withdrawn or lost to follow-up (at 6–12 months) will be replaced until the required sample size is obtained. Our previous bronchiectasis RCT^19^ reported a halving of respiratory exacerbations in the azithromycin group and the maximal benefit was achieved between 4 and 14 months of the intervention.^34^

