### Choice of duration of intervention

We chose two different durations of intervention (ie, 6 or 12 months of azithromycin/placebo) for two main reasons. First, we found previously the peak effect of using azithromycin for preventing bronchiectasis exacerbations occurred between 17 and 62 weeks^34^; thus, an intervention >4 months is justified. Second. while it would have been ideal to use a single intervention for 12 months, some parents/guardians declined to participate because they considered the intervention was too long. Thus, after recruiting five children, we altered the protocol so parents could choose either 6-month or 12-month intervention. Nevertheless, to date, just 2% of participants have opted out at the 6-month time-point.

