### Potential study limitations

First, heterogeneity exists between study sites but is reduced by including local community workers and having strict protocols for inclusion/exclusion criteria, data collection and measuring study outcomes. Further, randomisation is stratified, thus reducing the impact of any heterogeneity between sites. Second, directly observed medication adherence may not be possible in all participants. However, research or community health staff visit families weekly to dispense medications, and/or use medication logs with frequent phone contact, which should reduce the risk of non-adherence. Third, relying upon reviewing medical records risks missing some ALRIs if these records are incomplete.

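### The stated primary model leaves out the two randomisation strata (site and prior ALRI hospitalisation); if these are prognostic, the interval for the IRR is conservative

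*Protocol article*

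**What the plan says.** Protocol article, Randomisation, allocation concealment and blinding: sequences were generated in permuted blocks and each site holds two of them, "one stratified by site and the other by whether the child has had a prior ALRI hospitalisation or not".

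Potential study limitations: the article accepts that sites differ and answers that "randomisation is stratified, thus reducing the impact of any heterogeneity between sites".

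Primary aim: the analysis is a negative binomial regression reporting an IRR with a 95% CI, "including treatment group and the number of months taking treatment in the study included as an offset". Neither site nor prior ALRI hospitalisation is named there or in the secondary analyses. Data monitoring, management and analyses says that a detailed statistical analysis plan will be approved before the final analysis; it is not available here.

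**The concern.** Stratified blocks balance the arms within strata, so the estimated rate ratio varies less from trial to trial. A model-based negative binomial standard error reflects that gain only when the strata are in the model. Without them, differences between Darwin, Auckland and Dili, and between children with and without an earlier admission, are counted as unexplained dispersion. The interval is then wider than the design warrants and the test rejects too seldom. What is at stake is precision and some power, not validity.

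**Working it through.** **1. Inputs.** From Sample size: "We assumed a rate of three medically attended ALRI episodes per child-year in the control group", k=0.4, IRR 0.6, two-sided 5%, 90% power, 80 per group including 15% attrition. Design gives 1:1 allocation. Exposure is taken as one year, since "just 2% of participants have opted out at the 6-month time-point". Effects of site and prior hospitalisation on the event rate are not given and are assumed over a range.

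**2. The plan's own figure.** For two groups without covariates,

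n per group = (1.960 + 1.282)² × (1/r0 + 1/r1 + 2k) / (ln IRR)²

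With r0 = 3, r1 = 3 × 0.6 = 1.8 and k = 0.4, the bracket is 0.333 + 0.556 + 0.800 = 1.689, and n = 10.507 × 1.689 / 0.2609 = 68.0. Then 68/0.85 = 80, as stated. (Reading 0.4 as the reciprocal of the dispersion gives about 237 per group, so 0.4 is the dispersion.) The planned 90% is therefore the power of an unadjusted analysis with a dispersion of 0.4.

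**3. Analytic size.** If the strata explain a share s of k, the bracket for the adjusted model is 0.889 + 0.8(1 − s). At 68 per group:

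| s | Bracket | Unadjusted/adjusted CI width | Adjusted power |
|---|---|---|---|
| 0 | 1.689 | 1.000 | 90.0% |
| 0.10 | 1.609 | √(1.689/1.609) = 1.025 | 91.3% |
| 0.25 | 1.489 | 1.065 | 93.2% |
| 0.50 | 1.289 | 1.145 | 96.0% |

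**4. Simulation.** 136 evaluable children, blocks of 4 within site × prior hospitalisation (crossed strata are an assumption), maximum-likelihood Wald tests, 1500 runs per row. Overall dispersion is held at 0.4 through (1 + within-stratum k)(1 + CV²) = 1.4, where CV² is the squared coefficient of variation of the stratum rates. SE, SD and power are at IRR 0.6; type I error is from separate null runs.

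| Strata (CV²) | Within-stratum k | Unadjusted SE / true SD | Type I error, unadjusted v adjusted | Power, unadjusted v adjusted |
|---|---|---|---|---|
| None (0) | 0.400 | 0.157 / 0.158 | 4.5% v 5.4% | 90.9% v 91.1% |
| Mild (0.022) | 0.370 | 0.156 / 0.156 | 5.4% v 6.1% | 90.6% v 91.7% |
| Moderate (0.090) | 0.284 | 0.155 / 0.151 | 4.6% v 5.7% | 91.6% v 93.9% |
| Strong (0.238) | 0.131 | 0.155 / 0.131 | 2.1% v 5.3% | 95.0% v 97.8% |

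The mean IRR is about 0.60 with and without adjustment in every row. The true SD hardly moves with adjustment (moderate 0.151 v 0.150; strong 0.131 v 0.130): the blocks have already reduced it, and adjustment mainly brings the reported SE down to it.

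**5. Sensitivity to the assumed strata.** Other runs with different assumed effects agree in direction. Moderate: type I error 4.1% v 5.7%, power 91.0% v 93.5%. Strong: SE 0.145 against SD 0.131 (11% above), power 93.9% v 96.3%. Site rate ratios up to 0.6–1.6 with a prior-hospitalisation ratio of 1.5: SE up to 0.148 against SD 0.130 (14% above). The strong row above is the extreme, at 0.1549/0.1310, or 18% above. One further set with strong strata gave 91.8% v 95.7%, a gap of about 4 points.

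**6. If 0.4 is instead the within-stratum dispersion.** Overall dispersion becomes 1.4 × 1.090 − 1 = 0.53 (moderate) or 1.4 × 1.238 − 1 = 0.73 (strong). Power is then 88.8% v 91.1% and 82.7% v 88.7%, unadjusted v adjusted.

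**The case against.** **The analysis plan may add the terms.** The article condenses a fuller protocol, the analysis plan is still to come, and the model is described as including the listed terms, which does not rule out others. This stands as a limit on severity. It does not remove the point, because the article names the outcome, the distribution, the treatment term and the offset, and anyone fitting the model as written would leave the strata out.

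**The loss is conditional.** A reader might infer that the planned intervals are too wide and that power is being lost. The documents do not support that as fact. The nearest evidence is in the Introduction: ALRI hospitalisation of 427 per 1000 infants for Australia against 131 and 187 for New Zealand Māori and Pacific infants, ratios of 0.31 and 0.44. Those are population hospitalisation rates in infancy, not ALRI rates in children selected for a recent admission.

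**The stated power is not wrong.** A reader might also infer that 90% cannot be reached. It reproduces from the unadjusted formula, and falls short only if 0.4 is read as within-stratum dispersion, which the article does not say.

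**Stratification helps without adjustment.** Correct. Stratified blocks reduce the estimate's true variability whatever model is fitted, so the limitations paragraph is right as far as it goes. What is missed is an interval that shows the gain.

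**Part of the apparent power gain is not real.** Also correct. The adjusted Wald test ran at a type I error of about 5 to 6.5%. In one set of 3000 runs with moderate strata, power was 90.9% v 93.2% as tested but 91.9% for both once the tests were set to the same size. Only strong strata give a clear benefit.

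**Conclusion.** The point holds as a mismatch between design and stated analysis, with modest and conditional consequences. The IRR is not biased and the omission does not inflate type I error; any error is towards caution. With overall dispersion 0.4, the effect is negligible for no or mild stratum effects. It is roughly 2 to 3 points of power for moderate to strong effects, part of which reflects the adjusted test's slight liberality. With strong effects the model SE is about 10 to 15% above the true SD, or 18% under the most extreme assumption tried. All these sizes rest on assumed stratum effects, crossed strata and one year of exposure. The change is still worth making, since it follows the randomisation and costs almost nothing.

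**What to change.** In the analysis plan, before unblinding, specify the primary negative binomial model with treatment, site (four levels) and prior ALRI hospitalisation (yes/no) as fixed covariates plus the exposure offset. Use the same factors in the secondary regression models where event numbers allow. State in advance that the two Auckland hospitals are pooled if either is sparse.

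Because the adjusted maximum-likelihood Wald interval may under-cover slightly at about 136 children (type I error about 6%), use a small-sample correction or a likelihood-ratio test, or report the unadjusted model as a sensitivity analysis.

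In the randomisation section, state how the two lists at each site were formed. A list held within one site cannot itself be stratified by site; if the lists are for children with and without a prior ALRI hospitalisation, say so.

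The cost is a few lines of text. Both factors were needed to randomise, so no new data are required.

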### Data collection, monitoring and follow-up details

Data are collected by GCP-trained researchers using standardised data collection forms similar to our previous RCTs.^14 15 28^ At enrolment, sociodemographic, clinical and economic data and nasopharyngeal swabs (where possible) are collected (table 1). Sociodemographic details include age, sex, anthropometrics, family and household size, exposure to tobacco smoking (mother and household), breastfeeding, immunisation history, medications (prior to and during hospitalisation), current and previous ALRI history, comorbidities and the eight-item parent-cough specific quality of life (PC-QoL) score.^29 30^ Clinical data include respiratory symptoms/signs, investigations and treatments before and during hospitalisation. These details are obtained either by the parent/guardians and/or review of the child’s medical records.

**Table 1 T1:** Schedule of visits and contact points

		Month					
	Baseline (hospital)	1	4	8*	12*	18	24
Screening for eligibility	√						
Written informed consent	√						
Randomisation	√						
First dose of study medication	√						
Medical history	√						
Medical chart review	√	√	√	√	√	√	√
Clinical assessment _(where possible)_	√	√	√	√	√	√	√
PC-QoL	√	√	√	√	√	√	√
NPS†	√				√	√	√
Semistructured interview							√

* Will instead be done at 6 months for children opting out of the intervention at the 6-month time-point.

† For children living in remote locations in the unlikely event where the research team are physically unable to visit and/or other avenues have been exhausted, specimen collection will not occur in these instances.

NPSnasopharyngeal swabPC-QoLparent-cough quality of life

Medication adherence and adverse events (diarrhoea, vomiting, rash, nausea) logs are maintained either by the parents/guardian or research staff during the intervention period.

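### Adherence (≤ or >70%) is listed as a subgroup beside age, but it is a post-randomisation, largely parent-reported variable, so the within-stratum contrasts are not randomised and may be biased either way

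*Protocol article*

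**What the plan says.** Under Primary aim, after the negative binomial model, the protocol article says: "Subgroup analyses will be done for age (≤12, >12 months) and adherence (≤ or >70" (per cent). The two factors stand in one sentence, with no distinction between them.

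The section on randomisation, allocation concealment and blinding gives the source of the adherence measure: "Adherence is monitored by the research team in weekly medication logs based on parent reports". The data collection section adds, of the adherence and adverse event records, that "logs are maintained either by the parents/guardian or research staff during the intervention period". The limitations section concedes that "directly observed medication adherence may not be possible in all participants".

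The primary outcome is the "annualised rate of medically attended ALRIs during the intervention period of 6–12 months when the participants received the trial medications". The trial has two randomisation sequences, "one stratified by site and the other by whether the child has had a prior ALRI hospitalisation or not". For the main comparison the article says: "We will use an ‘intention-to-treat’ approach for the primary analysis".

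**The concern.** A subgroup analysis keeps the strength of randomisation only if the factor was fixed before allocation. Age qualifies. Adherence builds up afterwards, over the same months as the outcome, so two things can shape it besides the family's habits:

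- **The allocated treatment.** The secondary outcomes include "Adverse events (eg, nausea, vomiting, diarrhoea and rash"). Any of these could lower adherence more in one arm than in the other.
- **The outcome itself.** A family may stop dosing when ALRIs keep recurring, or may try harder.

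Children above 70% on azithromycin and children above 70% on placebo may then differ in underlying ALRI risk. Their rate ratio mixes any drug effect with that difference. At stake is how the >70% result is read: it looks like the effect of azithromycin when taken, but the design does not identify that effect from this contrast.

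**Working it through.** **Inputs from the article (Sample size).** Control rate 3 ALRIs per child-year, rate ratio 0.6 (so 1.8 on azithromycin), k = 0.4, two-sided 5%, 90% power, 80 per group including 15% attrition. Exposure is taken as one year; the article reports that only 2% have opted out at 6 months.

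**Inputs assumed.** 30% of children at ≤70% adherence, and the strength of the link between ALRIs and adherence. The article gives neither.

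**Step 1: the plan's own figure.** With variance μ + kμ², n per arm = (1.960 + 1.282)² × [(1/3 + 0.4) + (1/1.8 + 0.4)] / (ln 0.6)² = 10.507 × 1.689 / 0.2609 = 68.0. Then 68/0.85 = 80. The design reproduces, so k = 0.4 is used as the dispersion below.

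**Step 2: model for adherence.** ALRI count y is negative binomial with mean μ and dispersion 0.4. The chance of low adherence is L(y) = 1/(1 + exp(−(a + b·y))). Here b is the log-odds per ALRI, and a is set so that 30% of placebo children are low adherers. The mean count in the >70% stratum is Σ y·f(y)·(1 − L) / Σ f(y)·(1 − L); for ≤70%, replace 1 − L by L. The rate ratio in a stratum is the ratio of these means. The sums are exact, with no sampling error.

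**Step 3: no drug effect, same rule in both arms.** The stratum means are identical, so both rate ratios are 1.00. There is no bias.

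**Step 4: no drug effect, ALRIs drive low adherence on placebo only.** The azithromycin mean is 3.00 in both strata.

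| b | Placebo mean, >70% | Placebo mean, ≤70% | Rate ratio, >70% | Rate ratio, ≤70% |
|---|---|---|---|---|
| 0.15 | 2.691 | 3.720 | 1.12 | 0.81 |
| 0.30 | 2.423 | 4.347 | 1.24 | 0.69 |
| 0.50 | 2.170 | 4.936 | 1.38 | 0.61 |

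If the link exists on azithromycin only, the ratios invert: 0.90, 0.81 and 0.72 in the >70% stratum. The range for a null effect is thus 0.72 to 1.38. A milder difference (b = 0.3 on placebo, 0.2 on azithromycin, each arm at 30% low adherence) gives 1.07 and 0.91.

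**Step 5: true rate ratio 0.60 for every child, same rule (same a and b) in both arms.** ALRI counts now differ by arm, so one rule selects different children.

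| b | Azithromycin mean, >70% | Azithromycin mean, ≤70% | Rate ratio, >70% | Rate ratio, ≤70% |
|---|---|---|---|---|
| 0.15 | 1.671 | 2.164 | 0.62 | 0.58 |
| 0.30 | 1.570 | 2.580 | 0.65 | 0.59 |
| 0.50 | 1.476 | 3.139 | 0.68 | 0.64 |

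If low adherence is instead held at 30% in each arm with equal b, the >70% stratum gives 0.61 to 0.63 and the ≤70% stratum about 0.57.

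**Step 6: a second mechanism.** Suppose adherence depends on a child's underlying ALRI risk (gamma, variance 0.4), with a true ratio of 0.60 throughout. If the relation is the same in both arms and adherence is equal, both strata return 0.60. If it exists on azithromycin only, with 60% adherent there and 70% on placebo, the strata give 0.54 (>70%) and 0.70 (≤70%) for a log-odds of −0.5 per SD of log risk, and 0.67 and 0.50 for +0.5. Again the direction is not fixed.

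**The case against.** The strongest reply concerns size. Carers, those giving the drug and assessors are masked, the placebo matches in taste and appearance, and the article describes azithromycin as well tolerated. If the drug does nothing, families in both arms see the same ALRI pattern and have no reason to react differently; Step 3 then applies and the bias is nil. This stands: the 0.72 and 1.38 ends of Step 4 need a strong reaction in one arm and none in the other, which the blinding makes unlikely. It does not remove the point, because if the drug works, identical behaviour under full blinding still distorts the contrast (Step 5).

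A second reply is that intention-to-treat is primary and a detailed SAP is promised. Both are true. Exploratory labelling, caveats and interaction tests belong in an SAP, and their absence here is no fault. But the article does not leave the adherence split open: it fixes both the variable and the cut.

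A reader might go further and infer that the adherence result will be badly wrong, or that it would feed directly into prescribing. The documents support neither. They hold no data on adherence or its determinants, and they do not present the adherence split as confirmatory or as an estimate of efficacy when taken.

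Nor does it follow that a complier-average effect must replace it. That estimate would rest on the same parent-reported doses, needs an exclusion restriction and a dose-response assumption, and is not routine for overdispersed counts.

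**Conclusion.** The point holds as one of principle with a modest and uncertain size. Adherence is a post-randomisation variable, measured largely by parent report in the outcome window, and the protocol article lists it as a subgroup on the same footing as age. Contrasts within its strata are not randomised comparisons.

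Under the article's rate and dispersion, with 30% low adherence and b from 0.15 to 0.5 assumed:

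- the bias is nil with no drug effect and like behaviour in both arms;
- a true 0.60 reads as about 0.62 to 0.68 in the >70% stratum under one adherence rule for both arms;
- a null effect reads as about 0.72 to 1.38 in that stratum if only one arm's adherence responds to ALRIs, which is the extreme case.

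The direction cannot be known in advance, so a reader could not correct for it. The intention-to-treat primary estimate and the sample size are untouched.

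**What to change.** Before unblinding, take adherence off the subgroup list and keep age as the baseline subgroup. Report adherence descriptively by arm, saying how much rests on parent report.

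If an effect of treatment as taken is wanted, add one supplementary analysis that keeps the randomised comparison, for example a complier-average causal effect with randomised arm as the instrument. State the exclusion restriction, the dose-response assumption and the reliance on parent-reported doses. This part is optional.

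The cost is a change of wording, a little more analysis, and a wider confidence interval for the supplementary estimate. No new data are needed, and since the article says the SAP is still to be prepared and approved before the final analysis, the change can be made there.
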